### **3. Project Summary**

#### **3.1 Brief Summary**

##### **3.1.1 Introduction, background, objectives**

Thailand targets high risk groups for annual immunization with trivalent inactivated influenza vaccine (IIV3), including persons aged 65 years and older. However, there are few data from Thailand on the effectiveness of IIV3 in preventing influenza-associated illness and hospitalizations, and even fewer data on the cost-effectiveness of vaccination. This is a prospective population-based cohort study of persons aged 65 years and older that will compare the incidence of influenza-associated acute respiratory infection (ARI) and influenza-associated severe acute respiratory infection (SARI) between individuals who do and do not receive the influenza vaccine to measure the reduction in disease associated with IIV3. We will enroll and collect nasal self-swabs from randomly selected elderly each time they experience an ARI in two districts of Nakhon Phanom and test them for influenza. If they are hospitalized with SARI, a nurse will take a nasopharyngeal swab to test for influenza. Data on factors associated with vaccination will be measured and propensity for vaccination will be modeled in order to account for potential biases in the analysis. We will follow these elderly participants for two years and compare the number of influenza-associated ARI and SARI events between elderly that were vaccinated and elderly that were not vaccinated to calculate how effective IIV3 was in preventing influenza. This study will also evaluate the cost-effectiveness of IIV3 vaccine. Additionally, this study will measure the effect of having ARIs/SARIs on functional status, the VE of IIV3 in preventing influenza associated exacerbations among participants with chronic obstructive pulmonary disease(COPD), the duration of adequate IIV3 antibody levels in blood, and the incidence of respiratory syncytial virus (RSV) among the elderly.

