#### **7.1.5 Number of participants**

Sample size for cohort: The cohort sample size is calculated assuming a 50% vaccination rate, 80% power, a probability of committing a type I error of 5% and an incidence of influenza-associated ARI of 6% per year. With an expected VE of 40% based on our population's age and past studies (12, 16, 17), the required sample size is 2,724. Given a 15% loss to follow-up, a total of 3,133 persons should be enrolled, and assuming a 10% refusal rate, a total of 3,446, or, for simplicity, 3,500 individuals need to be selected

These sample sizes were calculated in OpenEpi.com(47) using the Fleiss Method with a correction factor as follows:

Fleiss Method:

$$n_1 = \frac{[Z_{\alpha}\sqrt{(r+1)\bar{p}\bar{q}} + Z_{1-\beta}\sqrt{rp_1q_1 + p_2q_2}]^2}{r(p_1 - q_1)^2}$$

$$n_2 = rn_1$$

where  $n_1$  is the number of cases and  $n_2$  is the number of controls,  $\bar{p}$  is the average exposure in the population,  $\bar{q}$  is  $1-\bar{p}$ ,  $p_1$  is the proportion of cases with the exposure,  $q_1$  is  $1-p_1$ ,  $p_2$  is the proportion of controls with exposure and  $q_2$  is  $1-p_2$ .

To account for the use of a normal distribution to approximate a binary function, a continuity correction is applied to  $n_1$  as follows to calculate the final sample size,  $n_{cc}$ :

$$n_{1cc} = \frac{n_1}{4} \left[ 1 + \sqrt{1 + \frac{2(r+1)}{n_1 r |p_2 - p_1|}} \right]^2$$

$$n_{2cc} = rn_{1cc}$$

where  $n_{1cc}$  and  $n_{2cc}$  are the corrected sample sizes of  $n_1$  and  $n_2$ , respectively.

Sample size for changes in functional status related to ARI or SARI: We will select matched pairs and compare functional status (measured on a 10 point scale by the VES-13) three-four weeks after the onset of an influenza-associated ARI or SARI to a control who has not had an ARI or SARI. As functional status is measured on continuous scale of 1-10, a matched dependent  $t$  test is used to compute sample sizes. We have used the PROC POWER procedure in SAS

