## **7.9 Data Analysis**

In order to evaluate the primary research question – the vaccine effectiveness of the inactivated trivalent IIV3 vaccine in the elderly - we will use Poisson regression with person-time at risk as an offset. The outcome variable will be the number of influenza associated ARI or SARI events in each given year of life among 2 groups, elderly who have been vaccinated with IIV3 and elderly who have not. The resulting count data will account for multiple outcomes in the same participant. We will also employ GEE methodology to the Poisson regression to account for geographical clustering by cases and correlation between outcomes in individuals with repeated measures. We can control for other predictive variables that may be associated with

underlying disease such as age, co-morbidities and distance to health facility. To reduce any potential non-random loss-to-follow up bias, we will use propensity score matching in addition to controlling for confounders. To address the other primary study question regarding cost, we will obtain estimates of direct and indirect costs from each of the groups and apply differences to the adjusted risks to arrive at the adjusted cost differences between elderly who have been vaccinated and elderly who have not been vaccinated.

In order to measure the effect ARI and SARI have on functional status (secondary objective 2.1) we will compare change in functional status among those that did and did not experience ARIs or SARIs by matching participants to one control when they become sick to see if there is a significant difference in functional status measurements. We will use a nested case control study to compare the two groups. By matching those who experienced a first ARI or SARI with those who had not on age ( $\pm 5$  years), sex, influenza vaccination and most recent functional status measurement ( $\pm 1$  point), we can account for unknown confounders that may cause a change in functional status while controlling for known confounders.

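### Section 7.9 uses propensity score matching against loss-to-follow-up bias, but the score described models vaccination and so addresses confounding; informative loss is left without a method

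*Protocol*

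**What the plan says.** Section 7.9 sets out the vaccine effectiveness analysis. For the primary question, "we will use Poisson regression with person-time at risk as an offset"; GEE is added for geographical clustering and repeated outcomes, with adjustment for variables such as age, co-morbidities and distance to a health facility. It then says: "To reduce any potential non-random loss-to-follow up bias, we will use propensity score matching in addition to controlling for confounders".

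Section 3.1.1 is the only place that says what the score models: "propensity for vaccination will be modeled in order to account for potential biases in the analysis".

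Section 7.1.5 expects material attrition. It inflates the sample size on the words "Given a 15% loss to follow-up", after a calculation for one year of incidence: "The cohort sample size is calculated assuming a 50% vaccination rate, 80% power", with "an incidence of influenza-associated ARI of 6% per year". Section 7.4 counts withdrawal, permanent moves and death as discontinuation.

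**The concern.** Section 7.9 names a bias, names a remedy, and the remedy is built for a different bias. A score for vaccination asks who gets vaccinated. Correcting for loss needs a model of who leaves. The sentence also sets matching apart from the control of confounders, so it reads as the plan's answer to attrition.

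The protocol gives reasons to expect loss that is not neutral. Section 4.2 notes that poor functional status may go with a higher risk of death and a lower chance of vaccination. The Limitations section says that sicker elderly people are more likely to be vaccinated. These point in opposite directions, but each links vaccination to underlying health, and death is itself one of the ways of leaving. Health also changes after baseline, which is why VES-13 is repeated every six months.

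At stake is the vaccine effectiveness estimate for objective 1.1. The cost comparison for objective 1.2 is also affected, because 7.9 builds it on the adjusted risks. The report would say that a bias had been dealt with when it had not.

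**Working it through.** **1. What each planned tool does about loss**

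| Tool in 7.9 | What it handles | What it leaves |
|---|---|---|
| Person-time offset | Unequal length of follow-up | Assumes loss is non-informative given the covariates |
| Covariate adjustment | Loss explained by those baseline covariates | Loss tied to later or unmeasured risk |
| Matching on vaccination propensity | Baseline confounding, and loss explained by covariates in the score | The same gap as covariate adjustment |

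The 15% inflation in 7.1.5 replaces numbers and does not remove bias. Section 7.9 names nothing else for informative loss.

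**2. Illustration of the gap (all parameters assumed)**

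The simulation used 25 runs of 40,000 people, a true rate ratio of 0.60, one measured covariate in the score, one unmeasured risk factor outside it, and 1:1 caliper matching. People who left contributed 0.2 of 2 years.

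| Loss mechanism | Share lost | Matched rate ratio |
|---|---|---|
| No loss | 0% | 0.60 |
| Depends only on the covariate in the score | 14.9% | 0.61 |
| Depends on vaccination and on risk outside the score | 14.7% | 0.48 |

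In the third row, high-risk people leave the vaccinated group and low-risk people leave the unvaccinated group. Vaccine effectiveness becomes 1 − 0.48 = 52% instead of 1 − 0.60 = 40%. The direction and size follow from that choice.

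**3. Power, if matching did replace the full-cohort analysis**

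Inputs from 7.1.5: 6% per year (taken as the unvaccinated risk), effectiveness 40%, hence 0.06 × 0.60 = 3.6%; half vaccinated; 5% type I error (two-sided assumed); 80% power; Fleiss with continuity correction. The difference p₁ − p₂ is used in the denominator, where the protocol prints p₁ − q₁.

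*The plan's figure.* With p̄ = 0.048:

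n = [1.96√(2 × 0.048 × 0.952) + 0.8416√(0.06 × 0.94 + 0.036 × 0.964)]² / 0.024² = 1,245 per group.

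n_cc = (1,245/4)[1 + √(1 + 4/(1,245 × 0.024))]² = 1,327 per group, 2,654 in all. The stated 2,724 is reproduced to within 2.6%.

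*Expected evaluable cohort.* 3,500 × 0.90 × 0.85 = 2,677, counting those lost as contributing nothing.

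*One-year power.* With n_cc = 2,677.5/2 = 1,338.75, inverting the correction gives n = (n_cc − 1/0.024)²/n_cc = 1,257. Power = Φ[(0.024√1,257 − 1.96 × 0.3023)/0.3018] = 80.4%.

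*Two years pooled.* Power = Φ[−ln 0.6/√(D(1/E₀ + 1/E₁)) − 1.96], with E₀ = 1,338.75 × 0.06 × 2 = 160.7, E₁ = 160.7 × 0.6 = 96.4, and D an assumed variance inflation for clustering.

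| Assumed discard | One year, corrected | One year, uncorrected | Two years, D = 1 | D = 1.5 | D = 2 |
|---|---|---|---|---|---|
| 0% | 80.4% | 82.8% | 97.8% | 89.9% | 80.1% |
| 10% | 75.9% | 78.7% | 96.4% | 86.7% | 75.8% |
| 20% | 70.5% | 73.9% | 94.4% | 82.5% | 70.8% |
| 30% | 64.2% | 68.1% | 91.3% | 77.3% | 65.0% |

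On the one-year basis, power falls below 80% once more than 1 − 2,654/2,677.5 = 0.9% is discarded (with correction), or 1 − 2,490/2,677.5 = 7% (without). The pooled columns assume that weekly surveillance runs for both years, as 6.2 implies; 3.1.4 describes weekly contact for one year.

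**The case against.** The sentence promises only to reduce the bias, and 3.1.1 speaks of biases in general, so the two sections do not contradict each other. If loss is non-informative given the covariates, person-time with adjustment is valid. Weekly contacts and the discontinuation rules supply the dates. An analysis plan not shown here may give the matching ratio, the role of the matched analysis and a treatment of censoring.

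Much of this stands, and it limits the point. A reader might infer that matching can do nothing about loss; the second row of the simulation shows otherwise. A reader might also infer that matching will cost the study its power. The documents do not support that. They give no matching ratio, caliper or replacement rule. They do not say that the matched analysis replaces the full-cohort model. They also plan on about 50% coverage in both districts (3.1.4, 7.1.5), where 1:1 matching with good overlap need not discard many people. Pooling two years restores a wide margin unless clustering is strong.

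What the objection does not answer is the stated purpose. Missing detail can wait for an analysis plan. A named remedy aimed at the wrong bias is an error in the protocol itself.

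**Conclusion.** Wrong as written. Section 7.9 gives a vaccination propensity score the task of reducing non-random loss bias. Beyond what covariate adjustment already provides, it does not do that task. Loss that depends on vaccination together with later or unmeasured risk has no planned method.

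The protocol does not allow the resulting bias to be sized or signed. The shift from 40% to 52% shows that about 15% loss can matter, under assumed and deliberately unfavourable parameters; it is not a forecast.

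The power point is secondary and holds only if matching replaces the full-cohort analysis. In that case the one-year margin is thin: about 80% at 2,677 evaluable, and about 76%, 70% and 64% after assumed discards of 10%, 20% and 30%. Pooled over two years, power is about 98% before clustering and about 80% with an assumed variance inflation of 2, with no discards.

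**What to change.** Reword 7.9 so that each problem has its own tool.

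- **Confounding:** assign the vaccination propensity score here, alongside covariate adjustment.
- **Loss to follow-up:** end each person's time at risk at the last completed weekly contact. Add a sensitivity analysis with inverse-probability-of-censoring weights, modelled from vaccination status, baseline covariates and the latest six-monthly VES-13 score.
- **Hierarchy:** state that the full-cohort Poisson/GEE model is primary and that any matched analysis is supplementary. This also settles the power question.

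The cost is a few sentences and one extra model, on data the protocol already collects. Extreme weights will need a truncation rule. The weights correct only for loss explained by what is measured, so the report should say that loss driven by wholly unmeasured risk remains an assumption.

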Influenza surveillance: Contact information, including phone numbers, will be recorded for all cohort participants. Health volunteers will contact all participants weekly for one year to identify any individual with new onset of cough or worsening of chronic cough, with or without fever (ARI) and any individuals with cough and fever  $\geq 38^{\circ}\text{C}$  requiring hospitalization (SARI). There are a number of diagnostic specimens that have been used to identify the viral etiology of ARI/SARI, including nasal, nasopharyngeal (NP) and oropharyngeal (OP) swabs. The most acceptable of these to patients is the nasal swab, as it is less invasive (1). Individuals with new onset of cough or worsening of chronic cough will be asked to take a nasal self-swab and properly store the sample in a separate tube. If the participant is too ill to be able to take a self-nasal swab, they will ask their assigned health volunteer to schedule a time to assist them in taking the swab. They will also be encouraged to seek medical attention at the sub-district health center, district hospital or provincial hospital where trained study staff is located if they are feeling very ill. The study will facilitate transport to the local health center for any severely ill participants who are unable to transport themselves. Trained research nurses in the hospital will take nasopharyngeal swabs for influenza diagnosis from admitted participants, and routine clinical information will be recorded. Nasopharyngeal swabs have been shown to be comparable to oropharyngeal swabs for detecting Influenza A and equal or superior to oropharyngeal swabs for detecting Influenza B (2, 3).

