In order to measure the impact of the first episode of ARI or SARI on functional status, we will conduct a nested case-control study of participants recovering from an ARI or SARI. Participants who experience their first ARI or SARI after enrollment will be matched with cohort participants who have not yet experienced an ARI or SARI based on age ( $\pm 5$  years), sex, influenza vaccination and most recent functional status measurement. Interviews will be conducted three to four weeks after the onset of ARI or SARI in the case and both cases and controls will be compared with respect to changes in functional status measurement (VES-13 score  $\geq 3$ ).

Elderly with COPD: In the standardized baseline questionnaire assessing functional status and medical conditions, participants will be asked whether they have been diagnosed with COPD. If they do, at the end of two years, the number of outpatient visits and inpatient admissions for exacerbations of COPD will be determined (by directly observing their medical records). A COPD exacerbation is defined as “a sustained worsening of the patient's condition, from the stable state and beyond normal day-to-day variations that is acute in onset and may warrant additional treatment in a patient with underlying COPD” (11). We will use the collected nasal self-swabs or healthcare worker collected nasopharyngeal swab taken when the participant was experiencing an ARI or SARI to confirm whether the COPD exacerbations the participant experienced were influenza-associated. At the end of the study, the incidence of all-cause COPD exacerbations and laboratory confirmed influenza-associated COPD exacerbations among the elderly with COPD who fit the ARI or SARI case definitions will be calculated. The incidence among those who were vaccinated will be compared to those who were not vaccinated.

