### **6.2 Duration:**

We will begin recruiting and training health care workers on data collection and laboratory technique in February of 2015 until April 2015 allowing three to four months. Participants enrolled in the study will be followed for two years from June 2015 through June 2017. Patients will be followed for two years as the incidence of influenza and the effectiveness of the annual vaccine composition can vary from year to year, making conclusions from two years more reliable than one alone. Additionally, approximately six more months will be needed for data analysis. The entire study will take place for approximately 2 years and 10 months, and should be completed by December 2017.

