To estimate the incidence of influenza-associated COPD exacerbations among elderly with COPD, we will calculate the total number of laboratory-confirmed influenza-associated COPD exacerbations per total number of COPD patients within our cohort over a year (primary objective 1.3). We will compare the incidence among those that were vaccinated with IIV3 versus those that were not vaccinated with IIV3. In order to account for correlation among repetitive measurements from each individual, we will also employ GEE methodology. This method will also allow us to adjust for underlying confounders such as smoking history and age.

Blood samples will be taken from a select number of participants who will have had IIV3 to test the antibody response of IIV3 among the elderly (objective 2.2). These blood samples will be taken at baseline before receiving the shot, and then again after 28 days (1 month), 180 days (6 months), and 360 days (12 months) later. The blood samples will be tested for HI antibodies. Everyone with a baseline HI assay  $\geq 10$  who has a four-fold increase in HI antibody count post vaccination or who has a baseline HI assay  $< 10$  who has a post vaccination count  $\geq 40$  will be considered seroconverted against influenza. One additional blood draw will be taken after 28 days of subsequent vaccination in the second year to compare the effect of prior vaccination on level of immunological response. We will use a random effects model (RE) to compare blood

samples at the post vaccination dates to the baseline HI assay to determine how long participants vaccinated with IIV3 retain an adequate number of HI antibodies. RE allows us to control for the differences in antibody count amongst all individuals across unequal intervals and obtain a mean distribution. This methodology will also allow us to control for confounders such as age and factors which make participants immuno-compromised.

We will also evaluate a simpler outcome, the incidence rate of RSV among elderly with ARI or SARI over the entire observation period (second-objective 2.3), which should be similar between those that were vaccinated with Influenza IIV3 and those that were not.

Aggregate results may be shared with relevant CDC programs in which the findings of this study may have immediate policy implications. Opportunities for publication will be sought.

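### Primary objective 1.3: the COPD exacerbation rate is defined per head with an annual label, which fits neither the two-year event collection nor the person-time analysis used for the main vaccine effectiveness result

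*Protocol*

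**What the plan says.** The protocol describes the rate for primary objective 1.3 in several places.

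- **Section 7.9, COPD paragraph.** The influenza-associated incidence is the number of laboratory-confirmed "COPD exacerbations per total number of COPD patients within our cohort over a year". The contrast follows: "We will compare the incidence among those that were vaccinated with IIV3 versus those that were not vaccinated with IIV3". For repeated events, "In order to account for correlation among repetitive measurements from each individual, we will also employ GEE methodology". The COPD paragraph names no distribution and no person-time. It writes out a formula for the influenza-associated rate only, although objective 1.3 in Section 5 also covers all-cause exacerbations.
- **Section 3.1.4, Elderly with COPD.** The record review comes late: "at the end of two years, the number of outpatient visits and inpatient admissions for exacerbations of COPD will be determined". At the end of the study the incidence of all-cause and "laboratory confirmed influenza-associated COPD exacerbations among the elderly with COPD who fit the ARI or SARI case definitions will be calculated".
- **Section 7.9, main VE analysis.** For influenza-associated ARI or SARI, "we will use Poisson regression with person-time at risk as an offset".
- **Follow-up period.** Section 6.2 states "Participants enrolled in the study will be followed for two years from June 2015 through June 2017". The surveillance text in 3.1.4 states "Health volunteers will contact all participants weekly for one year".
- **Exits.** Section 7.1.5 allows for 15% loss to follow-up. Section 7.4 ends participation at withdrawal, a permanent move or death.

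**The concern.** A per-head rate with an annual label needs a one-year counting window, or a stated rule for annualising. The protocol gives neither, and it collects the events over two years. The reported COPD incidence could therefore refer to one year, to two years, or to two years divided by two.

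A head count also gives every COPD patient the same weight, whether observed for two months or two years. The main VE analysis avoids this with person-time; the COPD rate as written does not, although people with COPD may well die or leave early.

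Vaccination can also fall inside follow-up. Follow-up starts in June 2015, a campaign is planned for 2015 (3.1.2), and the vaccination dataset is expected to be complete only in January 2016 (7.5.1, functional status). A head count cannot split one person's time at the date of vaccination. What is at stake is the absolute rate for a primary objective and, under the conditions worked out below, the vaccinated-unvaccinated contrast.

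**Working it through.** **Inputs from the protocol.** Two years of follow-up (6.2); 15% loss, influenza-associated ARI at 6% per year and expected VE of 40% (all 7.1.5). The 6% is stated for influenza ARI in the whole cohort, not for COPD exacerbations, and is borrowed here for illustration. It cancels from every VE figure below.

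**Assumptions.** Exponential loss over the two years; the split of losses between groups; the date of vaccination. The protocol gives none of these for COPD.

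**The plan's own figure.** No rate, sample size or power is stated for objective 1.3, so there is nothing to reproduce. As a check on the borrowed inputs, a continuity-corrected comparison of 6% with 3.6% (two-sided 5%, 80% power) gives 1,327 per group, 2,654 in total, against the stated 2,724. That is 2.6% apart, and it supports reading 6% as the unvaccinated rate.

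**Step 1: mean person-years per head.** With a proportion L lost over two years, h = -ln(1 - L)/2 and P = L/h. This gives P = 2.000 for no loss, 1.898 for 10%, 1.846 for 15%, 1.793 for 20% and 1.682 for 30%. Events per head = annual rate x P.

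**Step 2: the absolute rate, if two-year events are reported as annual.**
- No loss: unvaccinated 0.06 x 2.000 = 0.120, vaccinated 0.036 x 2.000 = 0.072; both are 2.0 times the annual rate.
- 15% loss in both groups: 0.06 x 1.846 = 0.111 and 0.036 x 1.846 = 0.066; both are about 1.85 times.
- If the 15%-loss figure is instead halved to annualise it: 0.111/2 = 0.055 against a true 0.060, about 8% too low.

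**Step 3: the contrast with equal follow-up.** VE = 1 - (0.036 x P)/(0.06 x P). P cancels and VE stays at 40%, whatever the period.

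**Step 4: the contrast with unequal follow-up (assumed).**
- Loss 20% unvaccinated, 10% vaccinated: 1 - 0.6 x 1.898/1.793 = 36.5%.
- Loss 10% unvaccinated, 20% vaccinated: 1 - 0.6 x 1.793/1.898 = 43.3%.
- The wider splits, 30/15 and 15/30, give 34.2% and 45.3%.

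**Step 5: vaccination inside the window (assumed two months into one year).** Per vaccinee, relative to the unvaccinated rate, 2/12 = 0.167 of an expected event falls before vaccination and 0.6 x 10/12 = 0.500 after it.
- All events of vaccinees counted as vaccinated: 1 - (0.167 + 0.500) = 33%.
- Only events after vaccination counted, over the full head count: 1 - 0.500 = 50%.

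**Step 6: the same cases with person-time.** In Step 4 each rate is divided by its own P and VE is 40% again. In Step 5 the vaccinated rate is 0.500/(10/12) = 0.6 times the unvaccinated rate, so VE is 40%, provided time before vaccination counts as unvaccinated.

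**The case against.** The strongest reply is that the annual wording in 7.9 can be read as a yearly or annualised incidence. Section 7.5.1 has nurses record when each COPD visit took place, so events can be assigned to years, and the end-of-study language in 3.1.4 may say only when charts are reviewed. On that reading the twofold error disappears. This stands: the doubling is a possible result of the text, not a necessary one. But the period still has to be stated.

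A second reply is that the comparison also uses GEE, and that an SAP, not shown here, could supply the distribution and offset. That is partly right. However, 7.9 does more than leave the denominator open. It states one, and an offset added later would depart from that formula.

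A third reply is that the bias is small beside sampling error. Borrowing the 7.11% COPD prevalence cited from Bangkok in 4.2 and the 6% rate gives 3,133 x 0.0711 = 223 patients and 223 x (0.5 x 0.06 + 0.5 x 0.036) = about 11 influenza events a year. A shift from 40% to 37% would be hard to see with so few events. This also stands, and it is a reason to keep the point in proportion.

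Four stronger readings are tempting and are not supported:

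- **That the one-year/two-year mismatch distorts the vaccinated-unvaccinated contrast.** It is a common factor and cancels (Step 3).
- **That the plan uses only COPD patients with ARI or SARI as denominator.** The phrase in 3.1.4 is loose, but objective 1.3 in Section 5 attaches the case definitions to the exacerbation, and 7.9 divides by all COPD patients in the cohort.
- **That a head count cannot handle a year in which someone skips vaccination.** A yearly head count can classify each person afresh each year; only vaccination within a year is left unresolved.
- **That the wording costs precision by discarding a year of events.** The protocol does not say it uses one year only, and that reading cannot hold together with two years of events reported as annual.

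**Conclusion.** The inconsistency holds. For a primary objective, 7.9 fixes a per-head denominator with an annual label, out of step with the two-year collection in 3.1.4 and with the person-time analysis set out in the same section.

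The absolute rate could be up to 2.0 times too high (about 1.85 times with 15% loss), but only if two-year events are reported as annual. The contrast is at risk only through unequal follow-up or vaccination during follow-up, and the bias can run either way: about 37% or 43% instead of 40% under 20/10 or 10/20 losses, and about 33% or 50% with vaccination two months into a one-year window. These sizes rest on assumed loss splits, exponential loss and an assumed vaccination date; they show what the wording permits, not what will occur.

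**What to change.** In Section 7.9, define both COPD rates, influenza-associated and all-cause, as events per person-year at risk among all cohort members with COPD over the full two years. Compare them with the Poisson/GEE model already planned for the main VE analysis, with log person-time as the offset and vaccination status updated by date, so that time before vaccination counts as unvaccinated.

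In Section 3.1.4, align the COPD text with objective 1.3 in Section 5: ARI or SARI is a condition on the influenza-associated event, not a restriction of the denominator. Also reconcile the one-year weekly contact in 3.1.4 with the two-year follow-up in 6.2, because the swabs taken at ARI and SARI episodes help to confirm the influenza-associated events.

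The cost is protocol wording. Person-time and vaccination dates are needed for the main VE analysis in any case, and visit dates are already to be recorded for COPD patients, so no new data collection is required.
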